### 3.1. Effect Evaluation

#### 3.1.1. BMI z-Score

A trained member of the research team will assess the weight, height and waist circumference of the children, using a standardized protocol. Standing height will be measured to the nearest decimal in centimetres (cm) using the Seca© 213 stadiometer (Seca, Hamburg, Germany), with light clothing and without shoes. Weight will be measured to the nearest decimal in kilograms (kg) using the Seca© Clara 803 (Seca, Hamburg, Germany), digital weighing scale. Heavy clothing and shoes will be removed before measurement. Waist circumference will be measured using the Seca© 201 (Seca, Hamburg, Germany), measuring tape. Only a thin vest or t-shirt between the measuring tape and skin will be allowed. A single measurement will be performed to assess height, weight and waist circumference. Anything unusual occurring during the measurements, such as not wanting to take off shoes or wearing heavy clothing, will be recorded to adjust for it during analysis. Height and weight measurements will be used to calculate BMI, which will be converted to a BMI z-score, adjusted for age and gender using a Dutch reference population (the Fifth Growth Study) [2].

Similar anthropometric measurements will be performed on one of the parents of each family participating in the family-based component, using the same protocol and measurement instruments. Weight and height measurements will be used to calculate BMI.

#### 3.1.2. Dietary Intake

The children’s dietary intake will be measured both at home and at the preschool. A 24 h dietary telephone recall will be conducted to assess dietary intake at home. Researchers and research assistants will be trained in following a dietary recall protocol and entering data in the Blaise© software (version 4.8.4.1767 (Statistics Netherlands (CBS), The Hague, the Netherlands)). Phone calls will be done in the evening adopting a structured protocol that divides a day into seven chronological eating moments: yesterday’s evening snack(s), today’s breakfast, morning snack(s), lunch, afternoon snack(s), dinner and evening snack(s). Parents will be asked to report food products consumed, starting with yesterday’s evening snack(s). Fruit, vegetables and snacks will be the major focus of the dietary recall. This meant that snacking moments were explored in detail, while the questions about main meals focused on fruits, vegetables and beverages only.

Details of each product will be requested, such as the kind, portion size, amount and preparation technique. Probing questions (e.g., did he/she drink something during dinner? Was this regular soda or diet soda?) will be used as memory cues to help parents record all products, including product details.

Blaise© (version 4.8.4.1767 (Statistics Netherlands (CBS), The Hague, the Netherlands)), a system used to administer computer-controlled questionnaires, will serve as the data entry software and contain child products (e.g., candy, fruit drinks) and child portion sizes (e.g., segments of fruit and a sippy cup) to match a child’s diet. It also will provide an ‘unknown’ option, an ‘other’ option and a comment section whenever the existing codes will not match. These will be recoded into existing or new product codes later in the process. Blaise was connected to The Dutch Food Composition Database, version 2016/5.0 (National Institute for Public Health and the Environment (RIVM), Bilthoven, the Netherlands) to assess nutrient composition.

At the preschool, the children’s dietary intake will be assessed using a dietary journal [17]. The teachers will record the intake of each child on a predefined list of the most commonly consumed food products and beverages at the preschool. Additional blank spaces will be available for any other food products consumed. Consumption will be recorded in number of units most common for the food product (e.g., parts for fruits/vegetables, pieces for sweets, cups for beverages).

For families participating in the family-based component, a short food frequency questionnaire on fruits/vegetables, sweets and snacks, and beverages will be part of the measurement diary, which will be provided with the accelerometer, to assess parental dietary intake.

#### 3.1.3. Physical Activity and Sedentary Behaviour

Children’s PA and sedentary behavior (SB) will be assessed using Actigraph GT3X+ (Actigraph, Pensacola, FL, USA) accelerometers, applying an adjusted wearing protocol [63]. Accelerometers will be placed on the right hip using an elastic belt. Children will wear the accelerometers for eight consecutive days during waking hours. Instructions will be given to remove the accelerometer for activities involving water such as bathing, showering and swimming. Parents will be provided with a measurements diary to record wear-time particularities, preschool attendance, and attendance at other childcare facilities.

PA and SB of one parent of the families participating in the family-based component will be assessed using Actigraph GT3X+ (Actigraph, Pensacola, FL, USA) accelerometers. The measurement protocol for the children also will apply to their parents.

#### 3.1.4. Questionnaires

The preschool teachers will be asked to complete a questionnaire on demographic variables and nutritional and PA-related practices (Child-care Food and Activity Practices Questionnaire, CFAPQ) [64]. All parents will be asked to fill out a questionnaire on demographics and other background variables. The parents of children in the family component will be additionally asked to fill out a questionnaire on nutritional and PA-related practices (Preschooler Physical Activity Parenting Practices questionnaire (PPAPP) [65], and Comprehensive Feeding Practices Questionnaire (CFPQ) [66]), family health climate (Family Health Climate Scale [67]), and physical home environment, based on the Environment and Policy Assessment and Observation-Self Report (EPAO_SR) [68]).

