## Abstract

The promotion of healthy energy balance-related behaviours (EBRB) is already important for children at a young age. Different settings, for example childcare and home, play an important role in the EBRB of young children. Further, factors in different types of environment (e.g., physical, sociocultural and political) influence their behaviours. SuperFIT (Systems of Underprivileged Preschoolers in their home and preschool EnviRonment: Family Intervention Trial) is a comprehensive, integrated intervention approach for 2–4 year old children. This paper describes the development and design of the evaluation of SuperFIT. The SuperFIT intervention approach consists of preschool-based, family-based, and community-based components. Intervention activities aimed at changing the physical, sociocultural and political environments in each setting and establishing an increased alignment between the settings. A quasi-experimental design was adopted with twelve intervention and nine control preschools to evaluate effectiveness. The primary outcomes were Body Mass Index (BMI) z-scores (objectively assessed height and weight), dietary intake (24 h recall), and physical activity (accelerometer) of the children. Further, the effects on the nutrition- and physical activity-related practices of preschool teachers and parents were evaluated (questionnaires). Intervention effectiveness was evaluated using linear mixed models. Process evaluation was performed using mixed methods; both quantitative (questionnaires) and qualitative (observations and in-depth interviews) measures were used. The comprehensive, integrated approach of SuperFIT is expected to support healthy EBRB in young children.

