The SuperFIT approach, as implemented in a pilot region, will be evaluated through an effect and process evaluation. The aim of the effect evaluation is to assess its effectiveness on the BMI z-score, PA, sedentary behaviour and dietary intake (primary outcomes) of children aged 2–4 years old from disadvantaged families in the Netherlands. In order to do so, a quasi-experimental design will be adopted, and the intervention group will be compared to a control group that does not receive the SuperFIT intervention approach. Changes in the sociocultural environment (i.e., nutritional and PA-related practices of preschool teachers and parents) and the physical environment will also be assessed. The aim of the process evaluation will be to gain insight into the processes supporting the development and implementation of SuperFIT. This will be used to better understand the results of the effect evaluation and support their interpretation. The current paper describes the content of the SuperFIT approach in the pilot region and the research protocol concerning the evaluation.

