## 3. Data Collection

For the effect evaluation, baseline measurements were performed before the start of the intervention, from January until April 2017. In the control group, baseline measurements were performed from January until July 2017. Follow-up measurements took place in November/December 2017 (first follow-up) and May/June 2018 (final follow-up). In order to reduce the participant burden, the data collection was aligned with intervention participation. This means that more elaborate data were collected for participants in the family-based component compared to participants in the preschool-based component or control group.

For the process evaluation, data were collected continuously during the implementation period. Qualitative and quantitative data will be entered, cleaned, coded and analysed from July 2018 until July 2020. Figure 1 shows the planning of the research and implementation of SuperFIT.

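### Parenting-practice questionnaires go only to family-component parents, so the effect on parents' practices announced in the abstract cannot be a controlled comparison

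*Protocol article*

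**What the plan says.** **What is promised.** The abstract says that "the effects on the nutrition- and physical activity-related practices of preschool teachers and parents were evaluated (questionnaires)". In the Introduction, the effect evaluation is set up so that "the intervention group will be compared to a control group that does not receive the SuperFIT intervention approach". It then adds: "Changes in the sociocultural environment (i.e., nutritional and PA-related practices of preschool teachers and parents) and the physical environment will also be assessed".

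**What is collected.** Section 3.1.4, which sits under the Effect Evaluation heading, gives every parent the same short form: "All parents will be asked to fill out a questionnaire on demographics and other background variables". It then adds the practice instruments (PPAPP and CFPQ), the family health climate scale and the home-environment items for one group only: "The parents of children in the family component will be additionally asked to fill out a questionnaire on nutritional and PA-related practices". Section 3 shows that this was deliberate and meant to limit burden: "more elaborate data were collected for participants in the family-based component compared to participants in the preschool-based component or control group".

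**What is analysed.** Section 3.3 describes a linear mixed model with child and preschool levels for the effects of the intervention. It describes no separate, uncontrolled analysis for parents. The limitations in section 4 mention the lack of randomisation and possible selection bias, but not a missing comparator for parents' practices.

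**The concern.** An effect of a programme on parents' practices needs parents who were not offered the programme and who answered the same questions. The text provides none. What remains is a before-and-after change in families who volunteered for the sessions.

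Such a change mixes the intervention with several other things: the child growing older, a different season, answering the same scales again, giving the answers the sessions taught, and regression to the mean. The mixed model cannot separate them, because no control observations enter it.

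This matters for interpretation because parents' practices are a direct target. Section 2.3.2 explains that the caregiver-only sessions were held so that influences such as parenting practices and screen-time rules could be addressed. A reported effect on them would be read as evidence that the home part of the approach worked.

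**Working it through.** The article gives no sample size, power or detectable difference for parents' practices (section 3.4 covers only child outcomes), so there is no figure of its own to reproduce. The check is a cross-reading and one count.

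**Step 1: who has practice data.**

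| Group | Background form (3.1.4) | Practice, climate and home scales (3.1.4) |
|---|---|---|
| Family-component parents | yes | yes |
| Preschool-only intervention parents | yes | no |
| Control parents | yes | no |

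Sections 2.3.2 and 2.5 offer the family component to families of the participating preschools and, later, to parents at other preschools in the pilot region. Restricting the scales to this component therefore excludes every control parent.

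**Step 2: the count.** Inputs: 99 intervention and 92 control participants, and 41.0% of consenting intervention parents also agreeing to the family component (all section 3.4). I assume one family per child.

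- Family component: 0.410 × 99 = 40.6, about 41
- Preschool-only: 99 − 41 = 58, with no practice data
- Control: 0 of 92 with practice data

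The 41 and 58 are approximations. The 41.0% describes initial recruitment, whereas section 2.5 reports further recruitment to the family component, including from other preschools. The zero for controls does not depend on the split.

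**Step 3: what can be estimated.** A controlled effect is

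(mean change, intervention) − (mean change, control).

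The second term has no observations, so only the first can be computed, and only in family-component volunteers.

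**Step 4: how much time the change spans.** Section 3 puts the intervention group's baseline in January to April 2017 and the final follow-up in May/June 2018. The shortest interval is April 2017 to May 2018, 13 months; the longest is January 2017 to June 2018, 17 months. Children enrolled between ages 2 and 4 are more than a year older at the end, and the final measurement falls in a different season from most of the baseline.

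**Step 5: contrast with teachers.** Section 3.4 reports that 65.0% of control teachers agreed to take part, and section 3.1.4 gives teachers their practice questionnaire without restriction by group. The teacher half of the abstract's sentence can be a controlled comparison; the parent half cannot.

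**The case against.** The strongest case against has four parts.

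- **Figure 1.** Its footnote lists practices, family health climate and home environment as content of the parental questionnaires, without naming a group. The figure is not shown and may say who received what. This stands as a caveat: a reader should not take it as proven that no control parent ever answered these scales. The footnote does not say that they did, however, and sections 3 and 3.1.4 are explicit and agree with each other.
- **The Introduction.** Its comparison with controls follows the primary outcomes, and for parents' practices it says only that changes will be assessed. Pre-post data could meet that. This also stands; a reader might infer that the Introduction promises a controlled parent comparison, but its wording does not require one. The conflict rests on the abstract's stronger claim of effects.
- **Burden.** The restriction is disclosed and has a reasonable motive. That justifies collecting less, but not claiming an effect from what was collected.
- **Scope.** A reader might extend the point to parental anthropometry, activity and diet, which are also limited to the family component, or to mediation. The article promises no effect evaluation of those parental measures and states no mediation analysis, so neither extension is supported.

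Nor is this a detail that an analysis plan could supply: no analysis can create control responses that were not collected.

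**Conclusion.** As sections 3 and 3.1.4 are written, the evaluation of effects on parents' practices announced in the abstract has no comparator. Family health climate and the home environment have none either, though the abstract makes no claim about them. The data would come from roughly 41 of 99 intervention families and 0 of 92 control families. They support a statement about change over time in volunteers and nothing about the difference from control.

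This rests on the text being complete about who received the scales, which Figure 1 could alter, and, for the 41 only, on the initial recruitment percentage.

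It would be wrong to infer that the effect evaluation as a whole lacks controls. Teachers' practices and the children's BMI z-score, diet and activity are not touched by this point.

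**What to change.** 1. Reconcile section 3.1.4 with the Figure 1 footnote by stating which groups received each parental questionnaire, and at which waves.
2. If control parents did not receive the scales, replace the abstract's claim of effects on parents' practices with uncontrolled within-group change in family-component parents.
3. In section 3.3, place this outcome outside the intervention-versus-control mixed model. Report it as pre-post change with confidence intervals and the actual number of parents contributing.
4. Add the missing comparator to the limitations in section 4, and state that these data will not be used to support an effectiveness claim.

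Giving the scales to control parents is no longer possible, because the last follow-up was in May/June 2018. The cost is therefore wording and analysis labelling, plus a weaker conclusion about parents' practices.

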#### 3.1.5. Preschool Physical Environment

Questions from the Environment and Policy Assessment and Observation instrument (EPAO) [69] related to the physical environment will be adapted to the Dutch setting and will be used to assess the physical preschool environment. A trained researcher will observe each location and will fill out the questionnaire at baseline and both follow-up measurements.

### 3.2. Process Evaluation

The process evaluation will be conducted to gain insight into the reach, adoption, implementation and maintenance of SuperFIT, using both quantitative and qualitative measurements. Preschool teachers and parents in the intervention group will be asked questions about their appreciation of SuperFIT in the follow-up questionnaires. Observations will be done at the preschool locations to assess implementation fidelity, change in daily activities, and the social and physical environment at the preschool. The observations were done in one morning, twice during implementation (September/October 2017 and April 2018) and once after implementation (September 2018).

In-depth semi-structured interviews were performed with the preschool teachers, parents, management, and implementers on several occasions during or following implementation. In June and July 2017, in-depth interviews were held with the preschool teachers, focusing on development and implementation. These interviews were also used to adapt the intervention strategies that were still to come.

In February and March 2018, in-depth interviews with the preschool teachers were held to gain insight into their experiences with SuperFIT, such as its strengths and limitations, and the facilitators and barriers of integrating SuperFIT into daily practice. Finally, in October and November 2018, in-depth interviews were held with preschool teachers, management and implementers that focused on the maintenance of SuperFIT within their organisation. After each round of the family-based component, in-depth interviews were held with the participating parents on their experiences, strengths and limitations, and changes that may have occurred as a result of their participation.

All intervention activities were observed using a free-form protocol to record any aspects occurring during the activities and give a general impression of the intervention activity. Attendance at the intervention activities was recorded in order to evaluate reach.

### 3.3. Data Analysis

Quantitative continuous variables will be presented as means and standard deviations. Categorical data will be presented by percentages of participants in each of the possible categories. Baseline characteristics and outcome values will be analysed for differences between the groups, using analysis of variance (ANOVA) for continuous variables and chi-square tests for categorical variables. The effects of SuperFIT will be analysed using linear mixed models with child and preschool levels in order to correct for repeated measurements and group effects. Known potentially relevant confounders will be taken into account based on the literature and/or differences in baseline characteristics. All analyses will be performed using SPSS version 25.0 (IBM Corp, Armonk, NY, USA).

Qualitative data of the interviews will be audio-recorded and transcribed verbatim. Interview transcripts will be coded by themes and concepts using NVivo version 11 (QSR International, Doncaster, Victoria, Australia).

### 3.4. Sample Size

An a priori sample size calculation was performed based on the BMI z-score. For the preschool-based component, the expected difference between the intervention and control condition was 0.10 BMI points [70]. Given a power of 0.90 and α < 0.05, a sample of 115 children in each group was required to detect this difference. Correcting for the potential nesting of effects within a preschool, considering an intraclass correlation of 0.0006, which corresponds to a design effect of 1.23, a total of 142 children should be included. Taking into account an attrition rate of 20%, 171 children should be included in each study group, resulting in 342 children.

For the family-based component, the expected difference between the intervention and control group is 0.30 BMI z-points [70]. Taking into account a power of 0.90 and α < 0.05, a sample of 38 families is required. Adjusting for an attrition rate of 30% a total of 50 families is the target for inclusion in the family-based component.

Recruitment for this study was done between January and April 2017 for the intervention group and between January and July 2017 for the control group. A flow diagram of participation is shown in Figure 2. Parents of 23.9% of the children attending intervention preschools agreed to participate in the preschool component, 41.0% of these parents also agreed to participate in the family-based component, and 26.7% of parents of children in the control preschools agreed to participate. Of the preschool teachers, 91.4% from the intervention preschools and 65.0% from the control preschools agreed to participate.

As the a priori calculated sample size was not reached, an additional power calculation was conducted. Based on the sample size (intervention *N* = 99; control *N* = 92), a difference of 0.19 BMI z- points can be detected, which seems attainable based on the available evidence [37,70]. The calculations are based on the same assumptions of the a priori sample size calculation. In addition, an increase of 1.44% of time in moderate-to-vigorous physical activity (MVPA) per day (corresponding to 8.91 min per day), 0.33 instances of fruit consumption per day, 0.26 instances of vegetable consumption per day, and 0.57 instances of water consumption per day can be detected. A decrease of 0.52 instances of sugar-sweetened beverages consumption per day and 0.61 instances of snack consumption per day can be detected. These differences also seem attainable based on the available evidence [59,71].

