### 2.5. Participants

A convenience sample of intervention preschools was recruited from a childcare organization in an urban municipality in Limburg (the Netherlands), based on the socio-economic status (SES) of their neighbourhood. Preschools could participate if they were located in the low-SES neighbourhoods of the pilot region. SES was based on the 2014 values of the Netherlands Institute for Social Research (SCP), with a negative score indicating a low SES [62]. Together with the management of the childcare organization, eligible preschools were selected. No other inclusion or exclusion criteria were applied. In total, twelve preschools participated in SuperFIT. Control preschools were selected in another urban area in Limburg in the south of the Netherlands. This area was comparable with regard to SES. One childcare organization collaborated, and a total of nine preschools participated as a control group. Due to the nature of the project, no randomization was performed. The Maastricht University Medical Centre, Medical Ethics Committee reviewed and approved this study (METC163022/ NL 58061.068.16), and the trial was prospectively registered (Clinicaltrials.gov, NCT03021980).

Children attending the participating preschools were eligible for inclusion. Additional inclusion criteria were: (1) at least one parent had to be able to understand Dutch, and (2) both parents signed the informed consent. Written information about the SuperFIT project was sent to each preschool to hand out to all parents with children attending that preschool. This information leaflet also informed the parents of the family-based component. Two weeks later, a researcher visited the preschool to explain SuperFIT verbally, starting with a kick-off event organised by the SuperFIT partnership. During that time, the parents were able to ask for additional information and hand in their informed consent for participation in the preschool-based component research and, additionally, the family-based component.

During the course of SuperFIT, additional recruitment efforts were made to increase participation in the family-based component. First, parents of the participating preschools were informed through newsletters of the new rounds starting the family-based components. Second, parents in other preschools in the pilot region were informed about the family-based component and invited to participate.

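### An intraclass correlation of 0.0006 cannot give a design effect of 1.23 for clustering by preschool, so the step from 115 to 142 children per group is unsupported as stated

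*Protocol article*

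**What the plan says.** Section 3.4 (Sample Size) starts from an unclustered requirement: "Given a power of 0.90 and α < 0.05, a sample of 115 children in each group was required to detect this difference". It then corrects for nesting of children within a preschool: "considering an intraclass correlation of 0.0006, which corresponds to a design effect of 1.23, a total of 142 children should be included". A 20% attrition allowance takes this to 171 per group and 342 in total.

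The article names no number of children per preschool for this step. Section 2.5 (Participants) gives the number of clusters: "In total, twelve preschools participated in SuperFIT" and "a total of nine preschools participated as a control group".

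The last paragraph of section 3.4 reports that the target was missed (99 intervention and 92 control children). It gives a new detectable difference of 0.19 BMI z-points and says that the a priori assumptions were kept. Section 3.3 (Data Analysis) plans linear mixed models with child and preschool levels.

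**The concern.** The ICC and the design effect are tied to each other through the number of study children per cluster. A very small ICC such as 0.0006 makes clustering negligible unless clusters are very large, whereas a design effect of 1.23 says that clustering costs nearly a quarter of the sample size. The sentence asserts both. Half-day preschools contributing a handful of study children each are nowhere near large enough to reconcile them.

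This is the only allowance for clustering in the sample size, so 142, 171 and 342 all pass through it. A reader cannot tell from the article whether the investigators judged clustering negligible or material. The later power statement says it rests on the same assumptions and so takes over the same ambiguity.

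**Working it through.** **Inputs.** From section 3.4: 115 per group unadjusted, ICC 0.0006, design effect 1.23, 142 after clustering, 20% attrition, 171 per group, 342 in total, achieved 99 and 92, participation rates 23.9% and 26.7%. From section 2.5: 12 intervention and 9 control preschools.

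**The plan's own chain.** 115 × 1.23 = 141.45, rounded up to 142. 142 × 1.20 = 170.4, rounded up to 171. 2 × 171 = 342. Everything after the design effect therefore reproduces as the authors did it. (Dividing by 1 − 0.20 would give 177.5, so 178; that is a separate matter.)

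**The step that does not reproduce.** Design effect = 1 + (m − 1) × ICC, with m study children per preschool. Solving for m: m = 1 + 0.23 / 0.0006 = 384. Allowing for rounding of both figures:
- lowest m: 1 + 0.225 / 0.00065 = 347
- highest m: 1 + 0.235 / 0.00055 = 428

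Even 347 exceeds the planned total of 342.

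**Design effect at ICC 0.0006 for other cluster sizes.** The article gives no m, so the first row is an assumption: the a priori target divided by the preschools that finally took part.

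| Basis | m | Design effect |
|---|---|---|
| 171/12 and 171/9 | 14.25 and 19 | 1.008 and 1.011 |
| 99/12 and 92/9 (achieved) | 8.25 and 10.2 | 1.004 and 1.006 |
| All attending children per preschool: 99/0.239/12 and 92/0.267/9 | 34.5 and 38.3 | 1.020 and 1.022 |
| One whole arm of 171 as a single cluster | 171 | 1.10 |
| All 342 children as a single cluster | 342 | 1.20 |

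The third row assumes that 99 and 92 are the numerators of the participation rates. Strongly unequal preschool sizes do not help: with a coefficient of variation of 1 and m = 19, the design effect is 1 + (2 × 19 − 1) × 0.0006 = 1.022. The only route I found to the neighbourhood of 1.23 is to treat every child attending anywhere in an arm, enrolled or not, as one cluster (99/0.239 = 414 gives 1.25; 92/0.267 = 345 gives 1.21). That is not nesting within a preschool.

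**If 0.0006 is right** (m of 14.25 to 19): 115 × 1.00795 = 115.9, so 116; 115 × 1.0108 = 116.2, so 117. With the article's × 1.2 this is 140 to 141 per group instead of 171.

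**If 1.23 is right**, the ICC needed is 0.23 / (m − 1):
- planned target: 0.23/13.25 = 0.017 and 0.23/18 = 0.013
- achieved sample: 0.23/7.25 = 0.032 and 0.23/9.22 = 0.025

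That is about 21 to 53 times the stated ICC.

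**Can the 0.19 settle which was used?** Keeping the a priori assumptions (0.10 detectable with 115 per group), the detectable difference with 99 and 92 children is 0.10 × √[(115/2) × (1/99 + 1/92) × DE]. The power, the significance level and the unstated standard deviation cancel.
- DE = 1: 0.110
- DE = 1.23: 0.122
- DE = 1.23 with a further 20% loss: 0.136

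None is 0.19. Without attrition, 0.19 would need a design effect of (0.19/0.1098)² = 3.0.

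**The case against.** The strongest reply is that the error may be confined to one printed number. Since 142 follows correctly from 115 × 1.23, a misprinted ICC would leave 142 intact. This stands. A reader might infer that 142 and 171 are too large, or too small, because of this sentence, but the documents support neither. They show that two figures conflict, not which one is wrong. If 0.0006 is the true figure, the clustering allowance was larger than needed, not smaller.

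A reader might also guess that 0.006 was meant, since 1 + 0.23/0.006 = 39 is close to the 35 to 38 children who seem to attend each preschool. That is conjecture. It rests on back-calculated attendance and would count all attending children rather than those studied. At 14 to 19 studied children, 0.006 gives only 1.08 to 1.11.

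A third tempting inference is that this contradiction explains the 0.19. It does not: 0.19 fails to follow from the a priori assumptions under either design effect, so that mismatch has a further, separate source.

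Finally, recruitment is complete, the shortfall is openly reported, and the mixed model in section 3.3 estimates clustering from the data. The stated ICC does not enter the effect estimates or their standard errors. This also stands and limits the consequence. It does not make the sentence true, and no fuller document could, because the article asserts the correspondence itself.

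**Conclusion.** The point holds as a contradiction between two stated figures. For clustering by preschool, ICC 0.0006 and design effect 1.23 are incompatible at any cluster size this trial could have. That conclusion needs no assumption about cluster size, because the required 384 (at least 347) exceeds the planned total of 342. The clustering step from 115 to 142, and with it 171 and 342, is unsupported as stated, though not shown to be wrong in value.

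The size depends on which figure is wrong and on the assumed 14 to 19 children per preschool. Either about 116 to 117 per group before attrition would have done in place of 142, or the ICC is really about 0.013 to 0.017 (0.025 to 0.032 at the achieved 8 to 10 per preschool). For the detectable difference, choosing 1.23 over 1.01 matters by √(1.23/1.01) = 1.10, about 10%. That is small beside the separate gap between 0.11 to 0.12 and the reported 0.19. The effect is on the sample size and power justification only.

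**What to change.** In section 3.4, state the ICC and the number of study children per preschool actually used, and compute the design effect from them. Carry the result through to the figures now given as 142, 171 and 342. If the ICC was misprinted and 142 stands, correct the ICC and give the cluster size that yields 1.23.

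Then recompute the detectable differences for 99 children in 12 preschools and 92 in 9 with the corrected design effect. State the remaining inputs, including the standard deviation, so that the source of the 0.19 can be seen. An allowance for unequal preschool sizes and a report of the ICC observed at baseline would be useful additions, but are not needed to resolve the contradiction.

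The cost is a recalculation and a few corrected figures in section 3.4. Conduct of the trial and the planned mixed-model analysis are unchanged.
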